### Randomization

An independent epidemiologist performed final randomization of the clusters, and allocation to control and intervention arms was revealed only after all study personnel were recruited and assigned to their respective clusters, and after initial community sensitization had occurred. Randomization codes will be broken only once the birth weight outcome data collection has finished.

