## Methods/Design

We hypothesize thatUse of clean cookstoves introduced before the third trimester of pregnancy will lead to a significant increase in average birth weight.Use of clean cookstoves starting before the third trimester of pregnancy will lead to a significant reduction in the risk of physician-assessed severe pneumonia within the first year of life.

We are testing these hypotheses in a cluster-randomized intervention trial involving 1225 maternal-infant pairs in the Kintampo North and South districts of Ghana, West Africa. Thirty-five rural communities were randomly assigned to one of two intervention arms, or to a control arm. Community-based fieldworkers identify pregnant women and enroll them into the study. Gestational age is determined via ultrasound (SonoSite Inc., Bothel, WA, USA) at the enrollment clinic visit [16].

In intervention communities, we distribute intervention cookstoves to pregnant women after enrollment, along with health insurance and an insecticide-treated bed net. The control group receives insurance and an insecticide-treated bed net at enrollment, and an efficient biomass cookstove at the completion of the postnatal follow-up period in the matched intervention communities. We assess real-time personal exposure to CO among all studied participants during pregnancy (four times each) and among the infants during the first year of life (three times each). We monitor subsets of mothers during pregnancy (once) and of the infants (once) for real-time and PM_2.5_ during one of the CO monitoring sessions.

We measure birth weight to the nearest gram using a Tanita BD 585 digital baby scale (Tokyo, Japan). We record the time elapsed between delivery and birth weight measurement, and only birth weights collected within 24 hours of delivery are considered valid. Birth length and head circumference are also measured, and a placental sample is collected for malaria assessment and archiving. Birth measures are obtained for both health facility and home births.

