### Study setting

The research builds on an established collaboration between Columbia University in the City of New York and the Kintampo Health Research Center (KHRC) in Ghana. KHRC provides substantial surveillance and research infrastructure to support GRAPHS [18, 19]. In particular, GRAPHS draws heavily on the Kintampo Health and Demographic Surveillance System (KHDSS), which provides the opportunity to identify pregnant women and follow them up using the KHDSS address system [19].

The study area comprises rural communities in the forest-savannah transition zone in the middle part of Ghana. Households in the study region typically cook on traditional three- stone fires. Wood is by far the dominant fuel, though some households use charcoal as a secondary fuel [20]. Outdoor cooking is prevalent during the dry season, but nearly all households also have enclosed or covered kitchen areas for wet season cooking. In pilot studies leading up to the current work, we found 24 h average PM_2.5_ exposure to be approximately 130 μg/m^3^ [20]. Per the KHDSS database, prevalence of smoking is about 10 % in all households in the study area. Cigarette smoking is very rare among women, as most smokers are men. We assess cigarette use among study participants and other household members via questionnaire.

A cluster was defined as a community or group of communities that:Is located in Kintampo North or South Districts (the core study area for KHRC)Is primarily rural (in practice, this excluded the 2 district capital communities that are made up of approximately 40,000 people);

A woman is eligible to participate in the study if she:Is in the first or second trimester of pregnancy (gestational age ≤ 24 weeks; this is to ensure that the intervention is actually delivered and in use by 28 weeks)Is carrying a live singleton fetus (twins and higher order multiples are excluded)Is the primary cook in her household; andIs a non-smoker.

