**Fig. 2 Fig2:**
[figure not shown]
Flow chart

In the efficient biomass cookstove arm – hereafter called the “BioLite arm” – households receive two BioLite HomeStove cookstoves (BioLite Inc., Brooklyn, NY, USA). These stoves burn freely available biomass fuels, but do so in a constrained L-shaped combustion chamber that increases heat transfer efficiency relative to traditional three-stone fires (more energy to the pot per unit of wood). In addition, a fan blows air into the combustion chamber, which improves the combustion efficiency of the system. A thermoelectric generator powers the fan, enabling use without a connection to an electrical grid. While some versions of the BioLite provide power via a Universal S Bus (USB) port, we opted for a version that optimizes combustion efficiency at the expense of USB power.

Study participants in the LPG arm receive a two-burner LPG stove manufactured in Ghana by the Ghana Cylinder Manufacturing Co. (Accra, Ghana). We chose that particular stove because it is readily available in Ghana, both for the current study and for potential future distribution. Enrolled households also receive timely deliveries of LPG gas at no cost to the participants. GRAPHS leased a 5000-kg LPG tank to ensure continuous supply. If households run low on LPG prior to a scheduled delivery, they can contact their fieldworker and the study will make a special delivery. Control arm participants use their own three-stone traditional stoves for the duration of the trial and will receive one BioLite stove at the end of the study period. All participants receive an insecticide-treated net (ITN).

Community-based fieldworkers visit households every week to check up on the intervention stoves and address any problems. In the control areas the community-based fieldworker visits take place as in the intervention arms, and are framed as checkups on the ITNs.

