We also started investigating an LPG intervention. LPG is very clean [33] and very convenient, but we were uncertain of its public health relevance given its high cost and limited availability in Ghana. In 2012 we learned, however, that Ghana had laid plans for a substantial program to increase access to LPG both in rural and urban areas [34] and that Ghana’s Ministry of Energy had initiated a “Rural LPG Program” that was delivering free cookstoves and subsidized gas to rural communities. This support from the government was sufficient to convince the GRAPHS team that LPG was indeed a germane alternative.

We remained convinced, however, of the need to include an efficient biomass arm. While our interactions with the Government of Ghana had persuaded us that LPG was worth testing, we remained hopeful that efficient biomass combustion would provide a substantially less costly intervention for future large-scale interventions. Between 2010 and 2012 BioLite developed a production model of their HomeStove, and we began pilot testing in spring 2012. Initial units proved unreliable, but after several iterations we were satisfied that the BioLite was robust to long-term use. We launched enrollment in fall 2013 when the first shipment of BioLite stoves reached our study area in Ghana.

Our intervention entails providing participating households with clean cookstoves and, in the case of the LPG intervention, with an adequate supply of fuel. As with many public health interventions, we cannot ensure perfect compliance. While we try to minimize use of the traditional three-stone fires in intervention households through weekly stove use encouragement visits, we have observed that many households continue to use traditional stoves for certain cooking tasks (a practice sometimes referred to as “stove stacking” [35]). We address this in three ways. As discussed below, we are currently undertaking a separate study to objectively quantify stove use across arms and to link it to household characteristics. Additionally, we carry out weekly questionnaire-based assessments of stove use; these data will be available as a covariate in our adjusted analyses of our main health outcomes. Third, we collect extensive personal exposure data, which capture emissions both from continued use of incumbent stoves and from other nearby sources. These data will be used to estimate exposure-response relationships for our main outcomes.

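### Fieldworkers who know the arm identify and enrol women on a rolling basis under open allocation, so who enters each arm may differ

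*Protocol article*

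**What the plan says.** All references are to the protocol article.

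- **Unit of randomisation** (Methods/Design): "Thirty-five rural communities were randomly assigned to one of two intervention arms, or to a control arm".
- **When the arm becomes known** (Randomization): "allocation to control and intervention arms was revealed only after all study personnel were recruited and assigned to their respective clusters". The second condition is that the reveal came "after initial community sensitization had occurred". These are the only two conditions given.
- **Who recruits** (Methods/Design): "Community-based fieldworkers identify pregnant women and enroll them into the study". Stoves are handed out after enrolment, in communities already allocated. Consent is individual and comes before enrolment (Consent and ethical approval).
- **What recruiters know** (Interventions): "Community-based fieldworkers visit households every week to check up on the intervention stoves and address any problems".
- **Timing** (Selecting intervention cookstoves): "We launched enrollment in fall 2013 when the first shipment of BioLite stoves reached our study area in Ghana". Recruitment was still open at submission (Trial status).
- **What women receive** (Methods/Design; Interventions): every arm gets health insurance and a treated net. The LPG arm adds a two-burner stove and free gas, and the BioLite arm adds two stoves. Controls receive one BioLite stove, at the end.
- **Eligibility** (Study setting): gestational age of at most 24 weeks, live singleton, primary cook, non-smoker. Gestational age comes from ultrasound, assigned by an obstetrician blinded to arm (Data collection and management).
- **Possible sampling frame** (Study setting): the KHDSS "provides the opportunity to identify pregnant women and follow them up using the KHDSS address system".
- **Analysis** (Analysis plan): run both with and without covariates. Neither version is named as leading.

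**The concern.** The concealment rule protects the posting of staff and the sensitization of communities. It does not cover the selection of participants, the step at which bias can enter a cluster trial that recruits individuals after allocation. Randomising communities balances communities; it does not balance women chosen once the arm is known.

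The benefits specific to an arm are very unequal, and with rolling entry a later woman may have neighbours who already have a stove and free gas. That can change how actively women are sought, how soon a pregnancy is disclosed, whether a woman is described as primary cook, and whether she agrees to join.

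If women drawn in by the stove differ in birth weight or infant pneumonia risk from women who would have joined anyway, the intention-to-treat contrast mixes the stove effect with a difference in who enrolled. The unadjusted estimate carries all of it.

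**Working it through.** The protocol gives no figure for this point, so there is none to reproduce. The check is first the order of events, then an illustration of size.

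**Order of events.** Communities are randomised, staff are posted and communities sensitized, the arm is revealed, and women are enrolled by fieldworkers who service the stoves. The text does not date the reveal against the first enrolment. However, stoves follow each woman's enrolment in a community already described as intervention, and enrolment began when stoves arrived. It follows that at least part of recruitment ran under open allocation, and the point needs no more than that.

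**Which criteria are exposed.**

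| Criterion | How established | Exposed to knowledge of arm? |
|---|---|---|
| At most 24 weeks | Ultrasound, assigned blind to arm | Dating: no. How early she presents: yes |
| Live singleton | Can be checked on the same scan (inference) | Little |
| Non-smoker | Questionnaire | Little; smoking is very rare among women here |
| Primary cook | No objective check stated | Yes |

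Fieldworker identification and the woman's consent come on top of these criteria.

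**Standard errors for birth weight.** Inputs from Power calculations: ICC 0.07, effects 0.32 SD (BioLite) and 0.40 SD (LPG), arm sizes 455 / 455 / 315. Inferred: 1225/35 = 35 women per cluster, so 455/35 = 13 control and 13 BioLite clusters, and 315/35 = 9 LPG clusters.

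SE = sqrt{ [ICC + (1 - ICC)/m] × (1/k1 + 1/k2) }, with 0.07 + 0.93/35 = 0.0966.

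- BioLite v control: sqrt[0.0966 × (1/13 + 1/13)] = 0.122 SD, 24 df
- LPG v control: sqrt[0.0966 × (1/13 + 1/9)] = 0.135 SD, 20 df

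**Assumed bias.** If a share s of LPG enrollees would not have joined under control, and they differ by g SD, the bias is s × g. With s = 5-20 % and g = 0.2-0.5 SD, the range is 0.05 × 0.2 = 0.01 SD to 0.20 × 0.5 = 0.10 SD. Both s and g are assumptions. The same range is applied to BioLite.

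**Two-sided 5 % error when the stove has no effect** (noncentral t, noncentrality = bias/SE):

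| Bias (SD) | BioLite | LPG | Share of planned effect (BioLite / LPG) |
|---|---|---|---|
| 0.01 | 5.1 % | 5.1 % | 3 % / 2.5 % |
| 0.05 | 6.8 % | 6.4 % | 16 % / 12.5 % |
| 0.10 | 12.4 % | 10.9 % | 31 % / 25 % |

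**Pneumonia, LPG v control.** The planned risks are 0.30 and 0.15. If the extra women have a risk of 0.20 or 0.40 instead of 0.30, the shift is s × 0.10. For s = 5-20 % that is 0.005 to 0.02 in either direction, or 3-13 % of the planned difference of 0.15.

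**The case against.** The strongest reply is that the article already contains real safeguards:

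- Gestational age is measured and assigned blind to arm.
- Control women have reasons to join: insurance, a net, a later stove, weekly symptom checks, and transport and help with care.
- Control communities get matching weekly visits.
- The trial relies heavily on the KHDSS, and fieldworkers may already work from its lists. That is operational detail a full protocol could hold.
- The choice of lead model may sit in an SAP that is not shown, and a screening table belongs with the results.

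Much of this stands, and it rules out several stronger readings:

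- *That eligibility is largely self-reported.* It is not. Two of the four criteria can be checked by ultrasound, and non-smoking excludes few women.
- *That the arm was known before any woman was recruited.* This is a strong inference, but the text does not date it.
- *That control women have no reason to come forward.* They do; the incentive is unequal, not absent.
- *That both primary outcomes are biased.* This is possible but not shown.

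The opposite inference is not supported either. The Randomization section also says "Randomization codes will be broken only once the birth weight outcome data collection has finished", which a reader might take to mean that allocation stays hidden during recruitment. The same section describes the reveal, and the stoves are visible. The sentence can hold only for people such as analysts, and should say so.

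The sequence itself survives. The article describes the KHDSS as an opportunity, gives identification to fieldworkers, and does not commit to inviting every listed woman. Blinded dating governs how a woman who presents is classified, not whether or when she presents.

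**Conclusion.** The concern holds as a design weakness, not as a demonstrated bias. Identification, time of presentation within the 24-week limit, primary-cook status and consent may differ by arm, and the stated concealment rule does not reach those steps.

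On the assumed range, the consequence for birth weight runs from negligible (error rate about 5.1 %) to material (10.9 % for LPG, 12.4 % for BioLite). The upper end needs, for example, one in five enrollees to be drawn in by the stove and to differ by half an SD. The calculation rests on the stated ICC, equal clusters of 35, the inferred 13/13/9 split and the assumed values of s and g. Neither the actual size nor the direction can be read from the document.

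The point merits action because the remedies are cheap.

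**What to change.** 1. **Recruitment.** For the remaining recruitment, have fieldworkers in all three arms invite every pregnant woman on a KHDSS-generated list, on one fixed schedule. If this is already the practice, say so. State that the change cannot reach women already enrolled. Asking about cooking before the stove is mentioned would add little once neighbours have stoves.
2. **Analysis.** Name as the lead intention-to-treat model the one adjusted for pre-specified variables fixed before stove delivery and already collected: ultrasound gestational age at enrolment, maternal and household characteristics, and baseline CO. Report the unadjusted model second. Keep placental malaria and weekly stove use, both of which the article mentions as covariates, out of this model, because they are measured after stove delivery. If the SAP already sets the lead model, check it against this. Adjustment removes only differences captured by the measured variables.
3. **Reporting.** Give numbers listed, invited, eligible and enrolled by cluster and arm.
4. **Wording.** State when the reveal took place relative to the first enrolment, and to whom the later code-break applies.

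Cost: coordination with KHDSS rounds, a screening log per cluster, and a change of procedure part-way through recruitment that must be documented. The analysis change needs no new data.

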### Exposure assessment

Our exposure assessment strategy is based on the mixture of our pilot experiences in Ghana, which indicated that area sampling was not predictive of personal exposures, the available funds, and the publication record at the time of writing the proposal, which indicated that personal CO can be a good predictor of personal PM_2.5_ exposure [25–27] and that at least 48 hours of sampling was necessary [28, 29]. Furthermore, McCracken et al. [28] have shown that the predictive power of CO for personal PM_2.5_ can be greatly enhanced by taking into account questionnaire data that gather data on other predictors of exposure. As such, our exposure design focuses only on collection of personal samples and questionnaire data.

We use small, lightweight Lascar CO monitors for personal sampling of all women and infants in the proposed study (Lascar Electronics, London, UK). Monitoring sessions last 72 hours each, and occur 7 times (at baseline prior to intervention, 3 additional times during pregnancy, and 3 times after the birth of the baby). The exposure team checks CO monitors using certified span gas every 6 weeks, and instrument-specific readings are adjusted to reflect any drift from accuracy. In addition, we carry out co-located PM_2.5_ sampling in a subset of approximately half of study mothers (1 pre-natal and 1 infant monitoring sessions) to calibrate CO against PM_2.5_. These sampling sessions are also 72 hours long and use the RTI microPEM (RTI International, Research Triangle Park, NC, USA), which provides both gravimetric and nephelometer measurements.

### Data collection and management

We collect questionnaire data via paper forms that are completed in the field by trained field staff. Questionnaires serve to collect data on covariates to include in final analyses and also to track study procedures. Supervisors collect forms from the community-based fieldworkers every week and manually check for completeness and consistency. All data entry is done in KHRC’s computer center, and is completed in duplicate. The trial management team resolves all queries.

Other data are gathered in the clinic. At enrollment, trained midwives perform an ultrasound scan in a clinic setting and submit images to the study obstetrician for quality review and gestational age assignment blinded to trial arm. The exposure team downloads real-time exposure data from the CO and PM_2.5_ devices in KHRC’s exposure lab, and exposed pre-weighed filters are shipped to Columbia University for post-weighing. Real-time exposure data are inspected for quality at time of download. We collect urine from study mothers concurrent with all exposure assessments, and ship aliquoted samples to the US Centers for Disease Control and Prevention for analysis of polycyclic aromatic hydrocarbons (PAHs), with the hope of eventually validating a biomarker of cook smoke exposure.

### Analysis plan

We plan to evaluate the impact of the interventions on birth weight and pneumonia using two methods. First, we will carry out intention-to-treat analyses for both birth weight (assessed as a continuous variable: grams at birth) and incidence of physician-assessed severe pneumonia (assessed as new cases per weeks of child observation). Second, we will carry out exposure-response analysis in which we pool data across arms and model how our outcome variables are related to exposure levels. We will use non-linear models that account for confounders and for clustering. Missing data will be imputed using standard multiple imputation techniques [30]. Both analyses will be carried out with and without adjustments for covariates. In particular, we will control for mother, household, and community characteristics. In the case of birth weight, we will also control for placental malaria.

In addition to these main analyses, we plan several subgroup analyses on our primary outcomes, including comparison of groups defined on residence type (compound versus freestanding households); proximity to main road; gestational age at recruitment; and density of other exposure sources. We also plan to carry out secondary analyses on other birth and health outcomes that we predict will respond to reduction in air pollution exposure.

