**Methods/Design:**

The Ghana Randomized Air Pollution and Health Study (GRAPHS) is a cluster-randomized trial that evaluates the efficacy of clean fuels (liquefied petroleum gas, or LPG) and efficient biomass cookstoves in the Brong-Ahafo region of central Ghana. We recruit pregnant women into LPG, efficient cookstove, and control arms and track birth weight and physician-assessed severe pneumonia incidence in the first year of life. A woman is eligible to participate if she is in the first or second trimester of pregnancy and carrying a live singleton fetus, if she is the primary cook, and if she does not smoke. We hypothesize that babies born to intervention mothers will weigh more and will have fewer cases of physician-assessed severe pneumonia in the first year of life. Additionally, an extensive personal air pollution exposure monitoring effort opens the way for exposure-response analyses, which we will present alongside intention-to-treat analyses. Major funding was provided by the National Institute of Environmental Health Sciences, The Thrasher Research Fund, and the Global Alliance for Clean Cookstoves.

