## Background

In recent years, global health advocates have come to see household air pollution (HAP) – exposure to air pollution in the home, primarily from cooking with solid fuels – as a prime target for interventions. According to one recent authoritative estimate, HAP accounts for 3.5 million avoidable deaths per year globally, and ranks fourth by disability-adjusted life years (DALYs) among modifiable risk factors [1]. Reliable evidence on the effectiveness of interventions is, however, sparse. Cleaner interventions cost more, and public health resources are scarce. In short, intervention planners need to know: *how clean is clean enough*? And, *what household energy technologies will get us there?*

The burden of disease from HAP arises when incomplete combustion of solid fuels (primarily wood, animal dung, and crop residue) in inefficient cookstoves emits substantial quantities of fine particles (specifically, particles less than 2.5 microns in diameter, or PM_2.5_), carbon monoxide (CO), and a host of other health-damaging pollutants [2]. Combustion may occur indoors, exposing all household members to high levels of air pollution, or it may occur outdoors, mostly exposing cooks and others who are near the fire. Regardless of the hearth location, average exposures are high [3, 4].

An extensive epidemiological literature links these exposures to adverse health outcomes. Systematic reviews and meta-analyses for child acute lower respiratory infections (ALRI) [5], chronic obstructive pulmonary disease [6, 7], lung cancer [6, 8], reduced birth weight [9], and cataract [6] all show evidence of an association with HAP. For cardiovascular disease, evidence for increased risk from biomass smoke exposure comes both from numerous observational studies [10] and from interpolating risks from tobacco smoke and ambient air pollution [11, 12]. Direct empirical evidence of causality is limited, however. Most studies have been observational and, therefore, vulnerable to uncontrolled confounding. In particular, solid fuel use correlates with poverty, and poverty is both difficult to measure and itself a driver of disease through myriad causal channels. Even the rare epidemiological studies that include plausible measures of poverty are prone to endogeneity that can arise from optimizing behavior by household decision-makers.

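### The Analysis plan lets a pooled exposure-response model, as well as ITT, evaluate the impact of the interventions, although only ITT is a randomised comparison

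*Protocol article*

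**What the plan says.** The Analysis plan section of the protocol article begins "We plan to evaluate the impact of the interventions on birth weight and pneumonia using two methods". It then names them:

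- ITT: "First, we will carry out intention-to-treat analyses for both birth weight" and for incidence of severe pneumonia.
- Exposure-response: "Second, we will carry out exposure-response analysis in which we pool data across arms and model how our outcome variables are related to exposure levels".

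It adds "Both analyses will be carried out with and without adjustments for covariates". The next paragraph puts both under one label: "In addition to these main analyses, we plan several subgroup analyses on our primary outcomes". The Abstract (Methods/Design) speaks of "exposure-response analyses, which we will present alongside intention-to-treat analyses".

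The section also says that the models will account for confounders and clustering, and that characteristics of mother, household and community will be controlled for. The article does not say what follows for the interventions if the two methods disagree.

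**The concern.** The opening sentence gives the same question, whether the interventions had an impact, to two methods that estimate different things. The ITT contrast compares randomised communities. The exposure-response slope mixes differences between arms with differences between women or infants in the same arm. Those within-arm differences come from stove stacking, behaviour and other nearby sources, as the Discussion itself describes.

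The Background says of earlier work: "Most studies have been observational and, therefore, vulnerable to uncontrolled confounding". It singles out poverty as a correlate of solid fuel use that is hard to measure. Supplying experimental evidence is the stated reason for the trial. A model exposed to the same weakness should not be listed as a way of answering the experimental question, least of all in a version with no covariates.

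At stake is the reading of a split result. If ITT is null and exposure-response is positive, the opening sentence gives an author or policy reader grounds to treat the second as a finding about the stoves.

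**Working it through.** The plan gives no figure for this point, so there is none to reproduce. The check has a textual part and a sizing part.

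**1. What each method estimates.** Let x be a wealth-type confounder with variance 1. Let exposure E = arm shift + b·x + noise, and birth weight Y = g·x + community effect + noise, with no stove effect and no exposure effect. Randomisation makes arm independent of x, so:

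- ITT contrast: expected value 0, whatever g and b are.
- Unadjusted exposure-response slope: Cov(E,Y)/Var(E) = g·b/Var(E), which is not 0 unless g or b is 0.

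If wealthier women have lower exposure (b < 0) and heavier babies (g > 0), the slope is negative. That is the direction the trial hopes to find.

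**2. Inputs.** From the article: 1225 pairs in 35 communities, so 1225/35 = 35 per community on average; ICC 0.07 for birth weight; arms of 455, 455 and 315, so 13, 13 and 9 communities at 35 each. Assumed, not in the article: g and b as tabulated, ICC 0.1 for x, and arm shifts in exposure of −0.8 SD (BioLite) and −1.5 SD (LPG).

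**3. Simulation.** 2000 trials per case, random-intercept GLS with known ICC, two-sided 5% t tests. Entries are the proportion rejecting.

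| g | b | g·b | Exposure-response, unadjusted | Exposure-response, adjusted for x | ITT LPG, unadjusted |
|---|---|---|---|---|---|
| 0 | 0 | 0 | 0.044 | 0.044 | 0.046 |
| 0.10 | −0.2 | −0.02 | 0.083 | 0.044 | 0.047 |
| 0.15 | −0.3 | −0.045 | 0.249 | 0.044 | 0.046 |
| 0.20 | −0.3 | −0.06 | 0.411 | 0.044 | 0.047 |

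A separate run of 1500 trials per case gave 9%, 28% and 45% for the unadjusted exposure-response test in the three confounded cases. The order of size is stable; the second digit is not.

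**4. Cross-check by formula.** With a residual exposure–outcome correlation r (assumed), λ = r·√(1225/DE) and P(reject) = 1 − Φ(1.96 − λ) + Φ(−1.96 − λ). DE runs from 1 to 1 + 34 × 0.07 = 3.38.

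- r = 0.05: λ = 0.05 × 35 = 1.75 gives 42% (DE 1); λ = 0.05 × 19.04 = 0.95 gives 16% (DE 3.38).
- r = 0.10: λ = 3.50 gives 94% (DE 1); λ = 1.90 gives 48% (DE 3.38).

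The same formula applies to an adjusted model if adjustment leaves a residual correlation of that size. The 4% in the table holds only because x was measured without error.

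**The case against.** The strongest reply is that the article as a whole leans toward ITT for efficacy and exposure-response for a different question. The end of the Background states two aims: the health effects of household air pollution, and the effectiveness of particular stoves. The hypotheses concern introducing stoves, and Power calculations treats only a binary treatment variable. The Abstract introduces exposure-response as an addition. Selecting intervention cookstoves and Exposure assessment challenges and goals tie the exposure data to dose-response relations and targets for future stoves. The label of main analyses may only separate these from the subgroup and secondary analyses. Ranking analyses, and choosing an adjustment set, are commonly left to an analysis plan, which is not shown here. All of this stands, and it limits the point to the sentence that assigns the intervention question to both methods. That sentence is a statement, not an omission, and it sits badly with those other sections.

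Three stronger readings are tempting and are not supported:

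- **That the plan would declare a stove effective on exposure-response alone.** No section says so. The exposure-response results are ones "which we will present alongside intention-to-treat analyses", so a null ITT would be in view, and confounders are to be modelled.
- **That any one of several p-values below 0.05 counts as success.** With two ITT contrasts and one exposure-response test, each in two versions, one outcome has six p-values. In the confounded cases at least one falls below 0.05 in 18%, 34% and 49% of simulated trials. The article states no such rule, and that count includes the two-arm multiplicity that Power calculations openly accepts. The two unadjusted ITT contrasts alone give about 8%. Leaving out only the unadjusted exposure-response test brings the total to 13–14%, against 12% with no confounding.
- **That choosing between adjusted and unadjusted ITT is a comparable problem.** In the simulation, taking either version for LPG moved the error only from about 0.047 to at most 0.055.

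**Conclusion.** The point holds as one of wording and interpretation. The Analysis plan names a partly non-randomised model as a way to evaluate the impact of the interventions, and such a model does not estimate that impact. The exposed part is mainly the unadjusted version: with no true effect it rejects in about 8% to 41% of simulated trials, while ITT stays near 5% per arm. Adjusted exposure-response is safe, at about 4%, to the extent that the confounder is measured well, and the Background doubts that poverty can be.

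These percentages rest on assumed confounding and exposure shifts and on 13, 13 and 9 equal communities. They cover birth weight only; pneumonia was not simulated. They show what modest confounding could do, and do not estimate what it will do here. The misassignment itself rests on the text alone.

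**What to change.** Replace the opening of the Analysis plan with wording to this effect:

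*The impact of the interventions is judged only by the intention-to-treat contrasts of each intervention arm with control, from one pre-specified model that accounts for clustering, either without covariates or with a fixed set of baseline covariates. Exposure-response is a secondary, non-randomised analysis of the relation between exposure and outcome. It is not used to claim that an intervention worked. Its confounder-adjusted version leads; the unadjusted version is shown as descriptive.*

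Either ITT model is acceptable provided it is fixed in advance. The restriction to baseline covariates matters because placental malaria (Analysis plan) and weekly stove use (Selecting intervention cookstoves) both arise after randomisation. Both can stay in supporting analyses.

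The change should be made before the randomisation codes are broken. It costs only wording: every planned analysis is still run and reported. The downside for the sponsor is that a positive exposure-response curve can no longer be presented as evidence of stove efficacy.
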